## B. Medical Record Investigation

- A research nurse will investigate the medical history (e.g., diabetes, hypertension, hyperlipidemia, heart disease, stroke, cerebral hemorrhage, chronic liver disease, chronic kidney disease, asthma, chronic obstructive pulmonary disease, musculoskeletal disease, digestive disease, neurological disease, and psychiatric disease), cancer diagnosis (e.g., carcinoma ICD-10 code and date of diagnosis), cancer treatment history, and plan for life-sustaining treatment at the respective medical institution at the time of patient registration.
- A research nurse will conduct the medical record survey of the respective medical institution at

3, 6, and 12 months of patient enrollment to investigate the status of cancer treatment, hospitalization, ER use, and the use of medical services by the severely ill patient from the time of the previous assessment to each time point, as well as the use of medical services one month prior to death in the case of a deceased patient. The following items will be investigated through medical record surveys.

|                                                                                                                                                                                                                                     | 3 Months | 6 Months | 12 Months |
|-------------------------------------------------------------------------------------------------------------------------------------------------------------------------------------------------------------------------------------|----------|----------|-----------|
| Cancer Treatment Status
Cancer Progression
Anti-cancer Treatment Plan
Other Treatment Plans                                                                                                                                | O        | O        | O         |
| Hospitalization at a Medical Institution
Date of Hospitalization and Discharge
Hospitalization Route (e.g., outpatient or ER)
Scheduled Hospitalization
Result of Hospitalization (e.g., discharge, transfer, or death) | O        | O        | O         |
| Use of the ER
Date of Use (month and year)
KTAS at the ER
ER Address
Result of the Use (e.g., discharge, transfer, or death)                                                                                            | O        | O        | O         |
| Critical Care Use
Date of ICU Admission
Date of Ventilator Support
Number of Cardiopulmonary Resuscitations                                                                                                                | O        | O        | O         |
| Death in Hospital
Date of Death
Place of Death (e.g., ward, ICU, or ER)
Cause of Death (based on the death certificate)                                                                                                    | O        | O        | O         |
| Medical Service Use 1 Month Before Death
Date of ICU Admission
Date of Ventilator Support
Number of Cardiopulmonary Resuscitations
Undergoing Anti-cancer Treatment                                                     | O        | O        | O         |

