| Hypotheses                                                     | 
 
1. Use of medical services, such as unscheduled hospitalizations and emergency room (ER) visits, will be significantly reduced among advanced cancer patients who receive home care education and participate in the HBMC intervention program as compared to the patients in the control group.
 
2. The quality of life (QoL) will be significantly higher, and the degree of symptom control will be significantly better among advanced cancer patients who receive home care education and participate in the HBMC intervention program than those in the control group.
 
3. The rate of establishing advance care planning will be significantly higher among advanced cancer patients who receive home care education and participate in the HBMC intervention program than those in the control group.
 
4. The mortality rate will be significantly lower among advanced cancer patients who receive home care education and participate in the HBMC intervention program than those in the control group.
 
 |
| Basis of the Study                                             | 
 
- The provision of home care environment-based intervention to patients with severe illnesses can significantly reduce readmission rates and improve survival rates compared to the provision of existing hospitalization and outpatient services (Malik et al., 2019).
 
- Symptom control is better when home-based palliative care services are provided to cancer patients (Gomes et al., 2013).
 
                                                                                                                                                                                                                                                                                                                                                                                                                                                                                                                                                                                                                               |

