|                    | 
discontinued
 
 
5. When a participant uses an inpatient or home-based hospice care services
 
6. When the suspension of participation in the clinical trial is deemed best for the participant at the investigator's discretion
 
7. When a participant does not cooperate with the physician in charge of the clinical trial or does not follow the physician's instructions
 
8. When the regulatory authority, ethics committee, or Institutional Review Board suspends the clinical trial
 
 
* The termination of the study for patients who discontinue the study is as follows.
 
 
- Reasons 1, 3, 4, 5, 6, 7, or 8: Continuation of the investigation of medical records and secondary linkage data (18 months) until 12 months after the enrollment or withdrawal of consent; the additional survey will be conducted only with the patient's consent
 
- Reason 2: Survey or investigation of medical records will not be possible until 12 months after the enrollment; secondary data linkage will be conducted
 
 
* When participation consent is withdrawn, the previously collected data of the patient will be discarded if the patient does not wish the data to be used in the study.
                                                                                                                                                                                                                                                                                                                                                                                                                                                        |

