## **9. Study participants' enrollment and initial assessment**

### **A. Patient's Registration for the Clinical Trial and Initial Assessment**

#### ***1) Patient Recruitment***

- Post the recruitment information in the outpatient and inpatient wards and public bulletin boards of the participating institutions. Explain the study to the patients and their guardians who meet the inclusion criteria in the outpatient or inpatient ward of co-investigators and

register consenting patients.

- Explain the study to inpatients, outpatients, and their guardians who meet all inclusion criteria and none of the exclusion criteria at each participating institution. Obtain written informed consent from the patients who agree to participate in the study. Similarly, obtain separate written informed consent from their guardians.
- The patient's unique identification information (i.e., resident registration number) will be collected on the consent form for participation in the clinical trial to collect secondary data. Patients will check a separate box for providing their consent to allow the access and use of their data (e.g., data from the National Health Insurance Service and Health Insurance Review and Assessment Service, Statistic Korea's data on death, and data from the Korea National Institute for Bioethics Policy).

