#### *2) Secondary Efficacy Endpoint*

- Domain 1: The secondary endpoints related to patients' use of medical services and critical care are described below.
  - Number of unscheduled hospitalizations within 6 months of study enrollment (continuous or count variable)
  - Length of hospitalization (total length of hospitalization; continuous variable)
  - History of hospitalization (dichotomous variable)
  - Number of ER visits (continuous variable)
  - Length of ICU hospitalization (total length of hospitalization; continuous variable)
- Domain 2: The secondary endpoints related to patients' quality of life and their satisfaction with the service are described below.
  - Patient's quality of life (EQ-5D; continuous variable)
  - Patient's degree of symptom control (ESAS; continuous variable)
  - Patient's emotional status (PHQ-9; continuous variable)

- Patient's satisfaction with the service (continuous variable)
  
- Domain 3: The secondary endpoints related to the patient's death and preparation of advanced directives are described below.
  - Survival after enrollment (days; continuous variable)
  - Length of ICU hospitalization within 1 month of the patient's death (total length of hospitalization; continuous variable)
  - History of anti-cancer treatment within 1 month of the patient's death (dichotomous variable)
  - Duration of ventilator support within 1 month of the patient's death (total number of days; continuous variable)
  - Preparation of advance directives or physician orders for life-sustaining treatment (dichotomous variable)
  
- Domain 4: The secondary endpoints related to guardians' quality of life and their satisfaction with the service are described below.
  - Guardian's quality of life (EQ-5D; continuous variable)
  - Guardian's emotional status (PHQ-9; continuous variable)
  - Guardian's burden of care (CRA\_K; continuous variable)
  - Guardian's care competency (continuous variable)
  - Guardian's satisfaction with the service (continuous variable)
  
- Domain 5: The secondary endpoints related to medical expenses are described below.
  - Direct medical expenses (continuous variable; KRW)
  - Indirect medical expenses (continuous variable; KRW)

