## **C. Follow-up of Suspended Participants**

- Investigation of the medical records and secondary data linkage will be performed on the suspended participants from the time of suspension to the end of the remaining scheduled follow-up period (18 months after the registration) until no longer possible due to the participant's death, failure to follow-up, or withdrawal of consent. Any case of a patient receiving additional HBMC services (e.g., other HBMC pilot projects) other than the one provided in this clinical trial after the completion of the study will be recorded in the care

reports.

- For participants suspended due to reasons other than death, the follow-up survey will only be conducted with those who consent to participate via a telephone call made by a research nurse.

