### ***4) Statistical analysis***

Definition of home-based medical service intervention group and study dropouts: Patients who provided informed consent to the selected home-based medical service intervention institutions and control group institutions are defined as the intervention group and control group, respectively. Based on the principle of group classification by intention-to-treat (ITT) that only considers the initial classification of intervention, omission of home-based medical service is still defined as the intervention group, which causes a bias that reduces the effects in the treatment group. Despite the study's design to conservatively estimate the effects in the treatment group, if significant differences are observed in the results among patients who withdraw consent or dropout during follow-up, data up to the point of withdrawal of consent or dropout will be used. Dropout rates will be analyzed and reported for each group.

The mean proportion of unplanned hospitalization will be compared between the intervention and control groups for the primary outcome. The mean of continuous variables and a fraction of dichotomous variables for each item in domains one to five will be compared between the two groups for the secondary outcome. A generalized estimation equation will be used to evaluate intra-group correlations to compensate for clusters of patients in the participating institutions. Survival after enrollment will be compared using the Kaplan-Meier curve and Cox proportional hazard model.

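### For patients without data linkage, the protocol specifies a death date only for in-hospital deaths up to month 12, which can bias the survival comparison if place of death or linkage differs by arm

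*Protocol*

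**What the plan says.** **Endpoint and analysis.** Hypothesis 4 in the overview reads "The mortality rate will be significantly lower among advanced cancer patients" receiving the programme than among controls. Section 12.A.2, Domain 3, lists "Survival after enrollment (days; continuous variable" as a secondary endpoint. Section 14.B.4 adds: "Survival after enrollment will be compared using the Kaplan-Meier curve and Cox proportional hazard model". The protocol names neither the death source that feeds this analysis nor a cut-off date.

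**Chart source (section 11.B).** "A research nurse will conduct the medical record survey of the respective medical institution at" 3, 6 and 12 months. Its death item is headed Death in Hospital and asks for date, cause and "Place of Death (e.g., ward, ICU, or ER".

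**Linkage source (section 11.C table and overview).** Vital status, date of death and cause of death are obtained to 18 months with no limit on place. Linkage is optional (section 9.A.1): "Patients will check a separate box for providing their consent to allow the access and use of their data".

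**Suspended patients.** For every suspension reason except death, the overview continues record investigation and linkage "until 12 months after the enrollment or withdrawal of consent", with 18 months in brackets after the linkage data. Section 13.C carries record review and linkage to the "end of the remaining scheduled follow-up period (18 months after the registration".

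**The concern.** The two specified sources do not cover the same deaths. Linkage sees any death, while the chart item sees a death in hospital, from one institution's records. Which source applies depends on a consent box, and the expected share of patients ticking it is not stated.

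This matters because the programme is meant to help patients stay at home, so it may shift deaths out of hospital. In unlinked intervention patients such deaths could go unrecorded, and observed mortality would fall with no true benefit. The opposite is also possible. Biweekly nurse calls (section 9.B.5) exist only in the intervention arm and may bring home deaths to light there more often than in control. The overview also exempts controls from the home-visit distance exclusion, so controls may live farther away and die elsewhere. The affected outcome is the one behind hypothesis 4.

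**Working it through.** **1. The routes by which a death can become known**

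| Route | Who | Place of death | Date of death specified? |
|---|---|---|---|
| Chart item, 11.B | all patients | in hospital, respective institution | yes, at 3, 6 and 12 months |
| Linkage, 11.C and 9.A.1 | those ticking the separate box | any | yes, to 18 months |
| Death as a suspension event, 13.A | all patients | any | no date or source item |
| Biweekly nurse calls, 9.B.5 | intervention arm only | any | no |
| Questionnaire contact by phone or email, 11.A | both arms at 3 months; controls at 6 months only with consent (overview) | any | no |

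For an unlinked patient, only the first row yields a specified death date. The last three may reveal a death, but not in a defined way and not equally often in the two arms.

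**2. Scale, by simple arithmetic**

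The protocol states no survival figure, so there is nothing to reproduce. All inputs here are assumptions: true 12-month mortality of 50% in both arms, out-of-hospital share of deaths *h* = 20% in control and 40% in intervention, unlinked share *u* equal in both arms, and missed deaths kept as alive.

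Observed mortality m = 0.5 × (1 − u × h). Apparent HR ≈ ln(1 − m_int) / ln(1 − m_con).

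| u | m control | m intervention | Apparent HR |
|---|---|---|---|
| 10% | 0.5 × (1 − 0.02) = 0.49 | 0.5 × (1 − 0.04) = 0.48 | ln 0.52 / ln 0.51 = 0.97 |
| 20% | 0.5 × (1 − 0.04) = 0.48 | 0.5 × (1 − 0.08) = 0.46 | ln 0.54 / ln 0.52 = 0.94 |
| 30% | 0.5 × (1 − 0.06) = 0.47 | 0.5 × (1 − 0.12) = 0.44 | ln 0.56 / ln 0.53 = 0.91 |

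If *h* is the same in both arms, m is the same and the bias is nil.

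**3. Scale, by simulation**

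Setup: exponential survival, true HR of 1, 100,000 patients per arm, Cox model, assumed 18-month mortality of 40%, 60% or 80%. Linked patients have every death captured to 18 months. Unlinked patients have only in-hospital deaths captured to 12 months and are otherwise censored alive at 12 months.

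| Linked, intervention / control | In-hospital share of deaths, intervention / control | Apparent HR over the three mortality levels |
|---|---|---|
| 80% / 80% | 80% / 80% | 1.00 |
| 90% / 90% | 70% / 90% | 0.98 |
| 70% / 70% | 70% / 90% | 0.92 to 0.94 |
| 50% / 50% | 70% / 90% | 0.86 to 0.91 |
| 80% / 0% | 80% / 80% | 1.24 to 1.31 |

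The first row combines horizons of 12 and 18 months, equally in both arms, and shows no bias. Rows two to four show a spurious benefit when place of death differs. The last row shows a spurious harm when linkage differs. The direction therefore depends on quantities the protocol does not give.

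**4. Suspended patients**

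The overview stops at "until 12 months after the enrollment or withdrawal of consent" and ties 18 months to the linkage data. Section 13.C takes records and linkage together to 18 months. Routine chart review in section 11.B ends at 12 months for everyone. Taken literally, section 13.C would give suspended patients a longer chart review than continuing ones; the overview would not.

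**The case against.** The strongest reply is that linkage is evidently the intended death source. The linkage table in section 11.C is presented as serving primary and secondary outcomes and lists vital status at every time point. For patients who die, the overview says record investigation is no longer possible and linkage will be done. If survival uses linkage alone, the sources are not mixed. A reader might infer that the plan pools chart and linked deaths, or that an unlinked patient who dies at home is counted as alive. The protocol says neither, and Kaplan-Meier and Cox both allow censoring at last contact. Source hierarchy and censoring dates are commonly left to the SAP.

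Three further points stand. The listed places are examples, and the overview's review of service use in the month before death is not limited by place. Reading sections 11.B and 13.C with the overview, charts to 12 months and linkage to 18 months for all is a coherent intention, so longer chart review for suspended patients alone is not a settled rule. And the hazard ratios rest wholly on assumed inputs.

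This does not dispose of the data-collection gap. Linkage remains optional, and a review of service use before death presupposes that the death and its date are known. An SAP can choose a censoring rule, but it cannot recover a death date that no form asked for.

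**Conclusion.** The concern holds as a conditional one. In patients who do not consent to linkage, deaths outside hospital have no specified date or source. The survival comparison is biased if two things are both true: place of death or linkage differs by arm, and unlinked patients without a recorded death are treated as alive. The protocol does not rule out either.

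No size or direction can be claimed. The illustrative hazard ratios run from 0.86 to 1.31 with no true effect, and they return to 1.00 when linkage and place of death are equal across arms. It would be tempting to say that the difference between 12 and 18 months itself biases the result. It does not: that is administrative censoring.

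The disagreement between the overview and section 13.C on suspended patients is a separate matter of wording to reconcile, with no demonstrated effect on the estimate.

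The issue should be corrected, because it touches a named hypothesis and the remedy is cheap. The primary endpoint is not affected by it.

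**What to change.** 1. Change the chart item in section 11.B from in-hospital death to death in any place, with date, place and source of information. Collect it at 3, 6 and 12 months in the same way in both arms.
2. State that survival uses linked vital status where available, to one common cut-off in both arms. Keep unlinked patients in the ITT analysis, censored at last documented contact, and add an analysis of linkage consenters only as a sensitivity analysis. Define last contact from sources that exist in both arms, because the biweekly calls would otherwise give later dates in the intervention arm. Section 11.C words the 12-month linkage for intervention patients, whereas the overview and section 9.A.1 set no arm limit; this must be settled for the common cut-off to work.
3. Reconcile the overview with section 13.C so that chart review follows the same schedule for suspended and continuing patients.

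The cost is one form item, a few sentences, and slightly earlier censoring of unlinked patients. Censoring at last contact does not remove all bias, since contact may stop because the patient has died; the sensitivity analysis is there to show how much this matters. Making consenters the main analysis set instead would depart from the ITT grouping and add consent selection to a non-randomised comparison, so it is better kept as the sensitivity analysis.

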### C. Secondary linkage data

Concerning patients in the intervention group who agree to provide secondary data linkage,

their National Health Insurance Service data will be accessed after more than 12 months of enrollment (Table 1). The relevant data will be used to investigate information on healthcare service use and direct medical cost up to 12 months after their enrollment. Data will be evaluated at 12 months to recalculate and utilize medical use and cost information at 3, 6, and 12 months. At 18 or more months after enrollment, all patients in the intervention study who provide consent for data sharing will be investigated for information on death, hospice use, healthcare service use before death, and advance care planning status. Table 1 shows the items to be investigated from the National Health Insurance Service data.

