| Efficacy Assessment | 
1. Data Collection
 
1) Questionnaire
 
 
- Patients and guardians in both the intervention and control groups will complete a questionnaire at the time of participant registration.
 
- Participants in the intervention and control groups will complete a follow-up questionnaire 3 months after registration.
 
- Participants in the intervention group will complete an additional questionnaire 6 months after registration. In the case of the control group, only those who will provide consent to participate in the additional questionnaire at 3 months will complete the additional questionnaire at 6 months.
 
 
2) Medical Records Investigation
 
 
- Medical records at medical institutions will be investigated at 3, 6, and 12 months after the patient's registration for hospitalization (number and dates of hospitalizations), critical care use (date of ICU admission, date of ventilator support, and number of CPR attempts), and emergency room use (number of emergency room visits) at each time point.
 
- In the case of death at 3, 6, and 12 months after registration, the deceased patient's use of medical services (hospitalization, critical care use, and emergency room use) within one month of their death will be investigated.
 
 
3) Secondary Data Linkage
 
 
- For patients who will provide consent to secondary data linkages, the hospitalizations, medical expenses, death, type of end-of-life medical services used, and the use of emergency room, critical care, and hospice between the time of registration and 12 months will be investigated when all patients have been enrolled for 12 months or longer.
 
- Death, information related to hospice use, and the type of end-of-life medical services used will be investigated when all patients have been enrolled for 18 months or longer.
 
- For patients who will consent to secondary data linkages, whether legal forms for life-sustaining treatments (e.g., advance directives and physician orders for life-sustaining treatment) have been completed and by whom will be investigated at 12 and 18 months of enrollment when all patients have been enrolled for 12 and 18 months or longer, respectively.
 
 |

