| Caregiver's indirect medical expenses                                                                                                                                                                                                                                                                                                                                                                                                                 |   | ⊙ | ⊙* |   | Patient questionnaire                         |

⊙ Both intervention/control groups, ● Only intervention group

\*Conducted in the control group only when consent is provided at 3 months after enrollment for evaluation at 6 months.

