## 12. Efficacy Endpoint Evaluation Criteria, Methods, and Interpretation

### A. Evaluation Criteria

#### *1) Primary Efficacy Endpoint*

- The proportion of patients with unscheduled hospitalization within 6 months of study enrollment
- Definition of an unscheduled hospitalization: hospitalization at a respective participating institution for acute treatments (excluding scheduled hospitalizations for anti-cancer treatments, operations, and procedures), hospitalization at other medical institutions other than the participating institutions, or **hospitalization of 4 weeks or less at a nursing hospital**

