### ***2) Secondary Efficacy Endpoint***

- For each item in Domains 1 through 5, the means of continuous variables of the intervention and control groups will be compared. Additionally, the proportions of dichotomous variables of the intervention and control groups will be compared.
- Post-enrollment duration of survival in the intervention and control groups will be compared using the Kaplan-Meier curve.

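### Section 11.C limits the insurance linkage to the intervention group, contradicting the rest of the protocol; if followed, admissions elsewhere would be captured unequally by arm, and satisfaction has no control data under either reading

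*Protocol*

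**What the plan says.** **Linkage.** Protocol section 11.C describes the National Health Insurance data up to 12 months with the words "Concerning patients in the intervention group who agree to provide secondary data linkage". Its 18-month sentence is worded differently: "all patients in the intervention study who provide consent for data sharing will be investigated for information on death, hospice use". That could mean one arm or the whole trial. The Overview (Efficacy Assessment, Secondary Data Linkage) has no arm restriction: "For patients who will provide consent to secondary data linkages, the hospitalizations, medical expenses, death". Section 9.A likewise seeks linkage consent, by a separate box on the form, from patients generally.

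**Primary endpoint.** Section 12.A counts acute admissions at the participating institution, "hospitalization at other medical institutions other than the participating institutions", and nursing-hospital stays of up to four weeks. Section 11.B gives the chart source: "A research nurse will conduct the medical record survey of the respective medical institution at" 3, 6 and 12 months. The table under 11.C is titled as the linkage plan for both primary and secondary outcomes.

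**Questionnaires.** The legend of the section 11.A table reads "Both intervention/control groups, ● Only intervention group". The intervention-only symbol marks the patient scales (EQ-5D, ESAS, PHQ-9) and the caregiver scales (EQ-5D, PHQ-9, CRA-K, preparation, competence, accomplishment) at 6 months. It also marks patient and caregiver satisfaction at both 3 and 6 months. Section 12.B states: "For each item in Domains 1 through 5, the means of continuous variables of the intervention and control groups will be compared". Section 12.A lists patient satisfaction in Domain 2 and guardian satisfaction in Domain 4.

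**The concern.** In a two-arm comparison each endpoint component should be looked for in the same way in both arms. Here one component of the primary endpoint, an admission elsewhere, is not routinely visible in the participating hospital's own records, and the section that specifies the linkage grants it to one arm. A data team working from 11.C would find outside admissions systematically in the intervention group and only incidentally in the control group. The intervention group would appear to have relatively more events than it should. That could hide a real benefit or, with no true effect, suggest harm.

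Two secondary consequences follow from the text. Under literal 11.C, direct medical expenses would have no control data, because the chart review in 11.B lists no costs. Under the 11.A table, satisfaction has no control data at any time, so a planned comparison cannot be carried out.

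**Working it through.** **1. Linkage rules side by side**

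| Place | Who is linked |
|---|---|
| Overview, Secondary Data Linkage | all consenting patients |
| Section 9.A, recruitment | consent sought from patients without arm limit |
| Section 11.C, 12-month data | consenting intervention patients |
| Section 11.C, 18-month data | ambiguous |

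The first two rows and the third cannot all be followed.

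**2. Reproducing the planned power**

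Inputs from section 6: 66 patients in each of 3 clusters per arm, ICC 0.015, alpha 0.05 (taken as two-sided), effect size 0.2. The event rates behind the 0.2 are not printed; 50% v 30% is an assumption.

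- Design effect: 1 + 65 × 0.015 = 1.975. Effective n per arm: 198 / 1.975 = 100.25.
- Difference in proportions, pooled null variance: SE0 = √(2 × 0.40 × 0.60 / 100.25) = 0.0692; SE1 = √((0.25 + 0.21) / 100.25) = 0.0677. Power = Φ((0.20 − 1.96 × 0.0692) / 0.0677) = Φ(0.95) = 0.829. The protocol prints 0.83007.
- At 57 per cluster the same method gives 0.800 against the printed 78.8%.
- On the log odds ratio scale: 0.847 / √(1/0.25 + 1/0.21) = 0.847 / 2.960 = 0.286; z = 0.286 × √100.25 = 2.87; power = Φ(2.87 − 1.96) = 0.82.

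**3. Effect of one-sided capture (illustration)**

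Let f be the assumed share of control patients with an event whose only unscheduled admission was elsewhere and unseen. Observed control rate = 50% × (1 − f), with capture in the intervention arm taken as complete. The documents give no value for f.

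| f | Control rate seen | Difference | Odds ratio | Power for benefit | Rejection if no true effect (50% in both arms) |
|---|---|---|---|---|---|
| 0 | 50% | 20 points | 0.43 | 0.83 | 5% |
| 10% | 45% | 15 points | 0.52 | 0.59 | 10.9% |
| 20% | 40% | 10 points | 0.64 | 0.32 | 29.5% |
| 30% | 35% | 5 points | 0.80 | 0.11 | 57.6% |

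The 10-point row on the log odds ratio scale: 0.442 / √(1/0.24 + 1/0.21) = 0.442 / 2.988 = 0.148; z = 0.148 × √100.25 = 1.48; power = Φ(1.48 − 1.96) = 0.32. The rejections in the last column are nearly all towards apparent harm.

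If outside admissions were missed equally in both arms, power would be 0.76, 0.68 and 0.60 for f of 10%, 20% and 30%, with no bias when there is no true effect. The damage comes mainly from the asymmetry.

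**4. Questionnaire rules for controls**

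| Place | Controls at 6 months |
|---|---|
| Section 11.A, text | complete it, without condition |
| Overview, Questionnaire | only those who consent again at 3 months |
| Section 11.A, table | the nine scales are intervention-only; the re-consent footnote is attached to caregiver indirect expenses alone |

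At 3 months the table marks all nine scales for both groups. Satisfaction is intervention-only at 3 and 6 months.

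**The case against.** The strongest reply is that one phrase in 11.C is out of step. The Overview and section 9.A have no arm limit, section 13.C continues linkage for suspended participants without naming an arm, and a linkage plan for the primary outcome implies both arms. This stands. A reader might infer that the primary comparison is biased as designed; the documents show a contradiction that becomes a bias only if 11.C is applied literally.

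A reader might also infer that outside admissions can be seen only through linkage. That is not established. The 11.B form has a line for hospitalization at a medical institution and records transfers, so charts may catch some in either arm, which would narrow the gap. Nor do the documents support treating the intervention arm's two-weekly calls as a second source of endpoint events: the items in section 9.B 5) do not include hospitalization, and nothing routes the calls into the endpoint.

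The size is also open to challenge. The only event counts printed are 40/198 and 20/198, about 20% and 10%. Against a 20% control rate, a 10-point loss would be half of all control events, so the illustration should not be read as a forecast.

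Finally, a reader might conclude that the quality-of-life and caregiver comparisons are lost. They are not: both arms complete these scales at 3 months, and section 12 fixes no time point. What survives is the contradiction on a source for the primary endpoint, the satisfaction comparison that cannot be made, and the unreconciled 6-month rule.

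**Conclusion.** The point holds as a contradiction with a conditional consequence. Section 11.C conflicts with the Overview and section 9.A on who is linked. If 11.C is followed as written, outside admissions would be captured more completely in the intervention arm, biasing the primary comparison against HBMC, and direct medical expenses would lack control data.

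The size cannot be estimated from the documents. The fall in power from about 82% to about 32% rests on assumed rates of 50% v 30%, an assumed 10-point loss of control events, full capture in the intervention arm, and a normal approximation that makes no allowance for having only three clusters per arm.

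Independently of how 11.C is read, patient and guardian satisfaction cannot be compared between groups under the 11.A table. The 6-month scales need one rule for controls; the 3-month comparison is unaffected.

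**What to change.** - Reword section 11.C so that the linkage covers patients in both groups who consent to it, and make the 18-month sentence equally explicit.
- State that outside and nursing-hospital admissions are identified for the primary endpoint from the same sources and by the same rules in both arms. Linkage should not be the sole source, since patients who decline it would then have this component unobserved.
- Report the linkage consent rate by arm, with a sensitivity analysis of the primary endpoint in linked patients.
- Reconcile the Overview, the 11.A text and the 11.A table on the controls' 6-month questionnaire. Name 3 months as the main between-group time point for the scales. If 6-month control data are collected, report them as coming from a re-consenting subset.
- Add satisfaction to the existing 3-month control questionnaire, or remove it from the between-group comparisons in section 12 and describe it in the intervention arm only.

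The cost is mainly protocol wording: section 9.A already provides for linkage consent from all patients, and the 3-month control questionnaire already exists. The downside is that the primary result waits for the linkage data, which the Overview schedules for when all patients have been enrolled for at least 12 months.
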